**Methods**: The study is composed of three parts: Part 1: a cross-sectional study with 1000 participants to assess the existing exposure risks due to wastewater and faecal sludge in directly exposed groups (includes 150 workers and 275 farmers), and partially and non-exposed groups as a control group (includes 575 communities members) with a specific focus on parasitic infections, skin diseases, eye diseases, and diarrhoeal episodes. The survey comprises of two components: (i) a questionnaire study to obtain health risk and health outcomes related to the exposure to wastewater and faecal sludge; and (ii) the collection of stool samples to determine the prevalence and the intensity of helminth (with the Kato-Katz method) and of intestinal protozoa infections (with the formalin-ether concentration technique); Part 2: a pathogen flow analysis to observe the variance of pathogen contamination at critical control points over time, we will assess existing operational monitoring data and analyse over a period of two month wastewater and faecal sludge for helminth eggs (modified Bailenger method) and intestinal protozoa cysts (formalin-ether concentration technique); and Part 3: a quantitative microbial assessment interlinked to the pathogen flow analysis to estimate diarrhoeal and parasitic infection risk and validate the results with the findings obtained under objective 1. Finally, with a subset of the stool and wastewater samples we will perform PCR for species detection and/or meta-genomic analysis in order to provide quantitative insights into microbial population based on sequence data.

**Expected results**: We will generate evidence and fill knowledge gaps on diseases outcomes related to the exposure to wastewater and faecal sludge. Based on these results we will be able to make evidence-based recommendations of the most appropriate combination of health protection measures to achieve context specific health base targets along the wastewater and faecal sludge chains and contribute to the sanitation safety plans processes. Hence, this study can help to promote the safe recovery and reuse of water and nutrients along these two waste chains and will benefit the planning of new wastewater and faecal sludge treatment plants and/or solutions in Kampala city.

Acronyms and Abbreviations

AIW Agro-industrial waste

BSTDW Bugolobi sewerage, treatment and disposal works

CCP Critical control points

Eawag Swiss Federal Institute of Aquatic Science and Technology

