Deduced to the specific objectives we assume that increased exposure to wastewater and faecal sludge results in higher infection rates of parasitic diseases and other water-related diseases outcomes. Therefore we intent to test following two hypotheses:

1. The difference in odds ratio is 2.5 or higher between highly exposed groups (people working along the wastewater and faecal sludge chain) and the people without an exposure to the two waste chains (control groups).
2. The helminth infection intensity decreases with the distance to wastewater treatment plant in Bugolobi and the Nakivubo swamp.
3. Methodology
   1. Study site

Kampala is the capital and largest city of Uganda with a resident population of 1,597,500 people who live on an area of 197 km² (UBOS, 2010). This population nearly doubles during the day due to people who live in the neighbouring areas and travel to Kampala on a daily basis. The city has a [tropical climate](http://en.wikipedia.org/wiki/Tropical_wet_and_dry_climate) but because of the high altitude (1,190 m above sea level) the average temperature (16°C -28°C) is relatively cool compared to other lower altitude East African settings. The main rain season is between March and May and the short rain season is between November and December. Rainfall ranges between 500 mm and 2500 mm and the relative humidity is between 70% and 100% (Figure 1) (IWMI, 2012a).

The specific study site will be around the WW and FS treatment plant BSTDW and the Nakivubo swamp. It is located in an urban context of Kampala and surrounded by high density neighbourhoods in between Nakawa and Makindye divisions. The plant is operated by the NWSC and was constructed prior to the 1940s by the British and subsequently extended during the periods of 1956/1958. The WW entering the plant is treated via primary (grit and detritus removal and primary sedimentation), and secondary processes (effluent: trickling filter system secondary sedimentation; and WW sludge: anaerobic digestion ponds and drying beds). The secondary treated effluent is then led through a natural wetland (Nakivubo swamp) where it is tertiary treated before it is discharged into Lake Victoria (Figure 2). There are plans that the BSTDW is put out of service within the next 4-6 years, and replaced by a new plant. At the moment, NWSC and KCCA are conducting studies to determine the most appropriate treatment processes for this context.

[figure not shown]

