To calculate the sample size we relied on the hypothesis 1. We conducted a logistic regression analysis having four exposure levels W1/W2, F1, C1 and C2. The highest exposure level is assigned to W1 and W2 (due to their daily exposure to raw and untreated WW and FS), the second highest to F (due to accidentally intake of contaminated water and soil), the third highest to C1 (e.g. due to frequent flooding events) and the lowest to C2 (Blumenthal and Peasey 2002; WHO 2006a). The number of persons in category W1 and W2 is assumed to be limited to 150, the number of F1 to 250, the number of persons in class C1 to 200 while the number of persons in class C2 could be as high as necessary (Table 1).

**Table 3** Selection criteria and potential numbers of exposure groups

| **No.** | **Definition of exposure group** | **Estimated number of individuals** |
| --- | --- | --- |
| 1. **W1** | Worker who operate and work at Bugolobi Sewerage Treatment and Disposal works | 30-50 |
| 1. **W2** | Worker who collect and transport the faecal sludge | 100-150 |
| 1. **F** | Farmers who working within the Nakivubo swap and are exposed to WW and/or FS | 250-500 |
| 1. **C1** | Community in proximity of the wetland but are no farmers | 10,000-20,000 |
| 1. **C2** | Community who live and work approximately 2 km away from the Nakivubo swamp and live ether east of the Port Bell road and west of Kibuli road and Tank Hill road. | 10,000-20,000 |

We aim at a power of 95%, in order to make sure that a reduction in effective exposure variance by 35% still leaves 80% power. Effective exposure variance is the variance of the 4-level exposure variable after regression on potential confounding variables (e.g. socio-economic status). With a variance reduction by 35%, the remaining exposure variance is 65% of the original value, so that the standard deviation after reduction is about 80% of the original exposure standard deviation. This increases the standard error by a factor of 1.25. If we have 80% power with the adjusted standard error (SE) 1.25*SE we may detect an effect of ln(odds ratio (OR)) = (1.96+0.84)*1.25*SE = 3.5*SE = (1.96 + 1.54)*SE. And 1.54 corresponds to slightly less than 95% power with the original unadjusted SE. Clearly, the factor limiting power most strongly is the relatively small size of the highest exposure group (W1, W2).

**Table 4** Results of the logistic regression analysis considering four exposure variable (C1, C2, F1 and W1)

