| Exposure Scenarios | Assumed prevalence rate for C2 | Assumed difference in Odds Ratio between W1/W2 and C2 | Assumed prevalence rates in  C1 / F / W1,W2 | Calculated sample size for each group  C1 / C2 / F1 / W1,2 |
| --- | --- | --- | --- | --- |
| **1** | 40% | 2 | 46 / 51 / 57 | 300 / 200 / 250 / 150 |
| **2** | 30% | 2 | 35 / 40 / 46 | 400 / 200 / 250 / 150 |
| **3** | 20% | 2.5 | 25 / 32 / 38 | 300 / 200 / 250 / 150 |

To anticipate for non-response or missing data, a margin of 25 participants for F, C1 and of 50 for C2 is added resulting in a final sample size of 1000 participants

In view of these considerations and calculations we will plan to conduct our study with the sample size calculated for the exposure scenario 3 (Table 2) and target the following number of people in each group: C1: 350, C2: 225, F1: 275 and W1 and W2 an excessive sample of 50 and 100, respectively and assume a prevalence rate of intestinal parasitic infections of 20% ( Kabatereine et al. 1997; Blumenthal and Peasey 2002;; WHO 2006b) in the lowest exposure group (C2) and an OR between the highest (W1, W2) and lowest exposure group (C2) of 2.5.

- - - 1. Sampling procedures

First, we will sensitise the worker (W1 and W2) study groups while meeting with representatives of each group (WW treatment plant operator, chairman of FS workers) and explain the aims and procedures of the study. Each of the representatives will be asked to prepare a list that contains the names, sex and age of their group members. We aim to select an excessive sample of the two groups approximately 50 for W1 and 100 for W2.

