    - - - 1. *Pre-testing*

To pre-test the questionnaire interviews with the tablet computer and the collection and analysis of stool samples in Kampala, Uganda. Each assistant will interview 3 people who work in the office or lab of BSTDW. The next day we will collect stool samples from the interviewed people and analyse it at the lab of the MOH.

- - - - 1. *Field editing of data*

Data will be entered directly into the data entry mask of the ODK from the assistants during the interviews.

- - - - 1. *Missing data*

Participants are free to not answer any questions or provide a stool sample, in such a case the data entry field will be marked as missing. To anticipate for non-response or missing data, a margin of 25 participants for F, C1 and of 50 for C2 is added resulting in a final sample size of 1000 participants.

- - - 1. Data management and statistical analysis
         1. *Data management*

Every evening the data collected with the tablet computers will be synchronized with a secure server from Swiss TPH in Switzerland where only the main investigators have access to. A random sub sample (100-150 samples) of the collected stool samples will be completely anonymized and transferred to Switzerland for pending polymerase chain reaction (PCR) for species detection and/or meta-genomic analysis in order to provide quantitative insights into microbial population based on sequence data.

- - - - 1. *Statistical analysis*

First, data cleaning will be carried out using STATA version 12. In a next step, descriptive statistics will be used to calculate the distribution of the above mentioned dependent and independent variables within each exposure group.

A first analysis is to test hypothesis 1. Hence, a multilevel regression analyses, adjusting for confounding, will be used to measure the associations between dependent variables (disease outcomes) and independent representing the exposure to WW and FS and to calculate Odds ratios to measure the strength of the associations and to compare the exposure groups.

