A second multilevel regression analysis aims to test the hypothesis 2, which expects a potential association between helminth egg counts and the distance to the water treatment plant and the Nakivubo swamp. We will define x as equal the distance from water treatment plant and Nakivubo swamp (1 = maximal distance and 0 = living or working directly at the plant or Nakivubo swamp). A true difference in average logarithmized egg counts of 0.8 individual standard deviations between subjects with x = 0 and subjects with x =1 would guarantee 95% power of finding a statistically significant association and would leave room for covariate adjustment. To verify the hypothesis we would assume that a difference of 0.8 standard deviations corresponds to a situation where the median egg count of the highest exposure group (with x=0) is at the 80^th^ percentile of the lowest exposure group (with x = 1).

- - - 1. Expected outcomes

With the cross-sectional study approach will create scientific evidence on the exposure risk to the WW and FS and are able to map the health risk along two waste chains in the Nakivubo area. Hence, we will test if the assumption made in hypothesis 1 and 2 are true to verify or falsify the hypothesis.

- - 1. Study design for objective 2

**Approach:** We will establish a PFA along the WW and FS chain around the BTWP and the Nakavibu swamp in Kampala. We will follow the pathogen concentration of faecal coliform, helminth egg and intestinal protozoa cysts over time.

- - - 1. Data collection

To establish a PFA we intent to use as a backbone of the model secondary data (e.g. obtained during the routine quality data collected by the BTWP (Table 3)) and will conduct a trend analysis for the pathogens and contaminations of interest (faecal coliforms, pH and other relevant parameters which can be obtained) over time. Additionally, we will analyse the WW and FS over a period of 2 months for helminth eggs and intestinal protozoa cysts.

**Table 7** Quality testing of WW at various sources within and around the Bugolobi sewerage, treatment and disposal works

| **Reported Data: 09.01.2013** | **Standard** | **Raw sewage** | **Final effluent** | **Nakivubo channel** | **Nakivubo wetland** |
| --- | --- | --- | --- | --- | --- |
| Ammonia –N (mg/l) | **10** | 43 | 12 | 8 | 10 |
| BOD_5_ (mg/l) | **50** | 465 | 122 | 134 | 288 |
| COD (mg/l) | **100** | 889 | 239 | 258 | 266 |
| Conductivity (nS/cm) | **1’500** | 1’049 | 1’097 | 998 | 1’025 |

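### Hypothesis 1 is worded as OR 2.5 or higher, to be verified or falsified, but the sample size gives power only against OR = 1, and the outcome and comparator are not fixed

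*Combined protocol and SAP*

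**What the plan says.** **Hypothesis.** Section 3 states that "The difference in odds ratio is 2.5 or higher between highly exposed groups" and "the people without an exposure to the two waste chains (control groups"). It names no disease outcome. The sentence before it speaks of parasitic and other water-related diseases.

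**Decision language.** Section 4.2.1.9 (Expected outcomes) says "we will test if the assumption made in hypothesis 1 and 2 are true to verify or falsify the hypothesis".

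**Sample size.** Section 4.2.1.2 opens with "To calculate the sample size we relied on the hypothesis 1". It aims at 95% power, so that 80% remains after a 35% loss of exposure variance. It chooses scenario 3 of Table 4: a 20% prevalence of intestinal parasitic infection in C2 and "an OR between the highest (W1, W2) and lowest exposure group (C2) of 2.5". Scenarios 1 and 2 in the same table assume an OR of 2.

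**Analysis.** Section 4.2.1.8.2 plans a multilevel regression "to measure the associations between dependent variables (disease outcomes) and independent representing the exposure" to wastewater and faecal sludge, with odds ratios to compare the groups. It gives no primary outcome, null value or decision rule. Section 4.2.1.6.1 lists all detected parasites, helminth intensity, fever, skin, eye and respiratory disease, and diarrhoea.

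**Comparator.** The abstract treats workers and farmers together as directly exposed, and the "partially and non-exposed groups as a control group (includes 575 communities members"). Section 4.2.1.1 describes C1 as exposed and only C2 as not directly exposed.

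**The concern.** The effect size assumed for planning has been written as the hypothesis itself. These are different questions. A study sized to distinguish 2.5 from 1 has little ability to show that an OR is at least 2.5, or that it is below 2.5. If the report must say whether Hypothesis 1 was verified or falsified, the data will usually not support either answer. A clear association smaller than 2.5 could be presented as a failed hypothesis.

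Because no outcome is named and the control group is described in two ways, what counts as testing Hypothesis 1 could also be settled after the results are seen. Hypothesis 1 is the basis of the sample size and the first planned analysis, so it should be decidable as written.

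**Working it through.** **1. The plan's own figure.** Section 4.2.1.2 gives ln(OR) = (1.96 + 0.84) × 1.25 × SE = 3.5 × SE = (1.96 + 1.54) × SE. The arithmetic is right, and 1.54 corresponds to 93.8% power, as the text says (slightly under 95%). The effect is counted in standard errors from ln(OR) = 0, so the null is OR = 1. The 1.96 implies a two-sided 5% level. Both are inferred, since neither is stated in words.

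The stated power reproduces on that reading. Take scenario 3 as printed (C1 300, C2 200, F 250, W 150), with equal log-odds steps from 20% in C2 to OR 2.5 in workers. The SE of the log OR across the full range is 0.224 and the noncentrality is (0.916/0.224)² = 16.7. A 3-df test then has 94.5% power. Multiplying the noncentrality by 0.65 gives 79.9%.

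**2. Inputs for the planned contrast, W1/W2 v C2.**
- Workers: 150.
- C2 prevalence: 0.20. Worker prevalence at OR 2.5: odds 0.25 × 2.5 = 0.625, so 0.625/1.625 = 0.385 (Table 4 rounds to 38%).
- C2 size: 200 in Table 4, 225 in the text below it, 350 in Table 6. A size of 300 is added for the case that the C1 and C2 columns of Table 4 are exchanged; with the stated margins of 25 and 50 that would give Table 6's 225 and 350.
- SE = √[1/(n_C2 × 0.2 × 0.8) + 1/(150 × p_W × (1 − p_W))], unadjusted and without clustering.

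**3. True OR of 2.5.** On the log scale the estimate is centred on ln 2.5. It is therefore at least 2.5 in about 50% of studies, and the lower 95% limit exceeds 2.5 in 2.5%, whatever the sample size. The OR needed to exclude 2.5 with 80% power solves OR = 2.5 × exp(2.8 × SE), with the SE taken at that OR.

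| C2 | SE | Power v OR = 1 | 95% CI if 2.5 is observed | True OR for 80% power to exclude 2.5 |
|---|---|---|---|---|
| 200 | 0.244 | 96.4% | 1.55 to 4.03 | 4.9 |
| 225 | 0.237 | 97.2% | 1.57 to 3.97 | 4.8 |
| 300 | 0.221 | 98.5% | 1.62 to 3.86 | 4.6 |
| 350 | 0.215 | 99.0% | 1.64 to 3.81 | 4.5 |

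**4. True OR of 2.0** (the value assumed in scenarios 1 and 2; here with C2 at 20%, so worker prevalence is 0.5/1.5 = 0.333).

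| C2 | SE | OR = 1 rejected | Estimate below 2.5 | Upper 95% limit below 2.5 |
|---|---|---|---|---|
| 200 | 0.248 | 80% | 82% | 14% |
| 225 | 0.240 | 82% | 82% | 15% |
| 300 | 0.226 | 87% | 84% | 17% |
| 350 | 0.219 | 89% | 85% | 17% |

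**5. Which contrast carries the 2.5.** With Table 4's scenario 3 rates (C2 20, C1 25, F 32, W 38%) and sizes:
- W v C2: (0.38/0.62)/(0.20/0.80) = 2.45, which is 2.5 apart from rounding.
- W+F: (250 × 0.32 + 150 × 0.38)/400 = 0.3425. Against C2 the OR is 0.521/0.25 = 2.08.
- C1+C2: (300 × 0.25 + 200 × 0.20)/500 = 0.23. W against this is 0.613/0.299 = 2.05, and W+F against this is 0.521/0.299 = 1.74.

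Under the other allocations, and with unrounded rates, the pooled contrasts run from about 1.7 to 2.2.

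**The case against.** Section 4.2.1.8.2 plans adjusted odds ratios as measures of strength of association and states no rule against 2.5. On that view the threshold wording is loose and the study will report sensible estimates anyway. The stated power against OR = 1 reproduces, and recruitment and data would not change. This limits the harm but does not remove it: Sections 3 and 4.2.1.9 still promise a verdict on 2.5 that the design cannot deliver.

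Three stronger readings are tempting and are not supported.

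- *A doubling of the odds would be reported as falsifying Hypothesis 1.* The documents give no decision rule. The 82–85% in step 4 applies only if a point estimate below 2.5 counts as failure. If the confidence interval must exclude 2.5, the figure is 14–17% and the usual result is inconclusive. A true OR of 2.0 does contradict the hypothesis as worded; the trouble is that a clear association might be presented as a failure.
- *Hypothesis 1 is false under the plan's own assumptions.* That is so only for pooled contrasts. No analysis section pools C1 with C2 or workers with farmers, and Section 4.2.1.2 attaches 2.5 to W1/W2 v C2. The abstract describes the sample. Ambiguity remains, because people working along the chain could include farmers and the timetable in Section 7 labels both C1 and C2 as control groups.
- *The several outcomes imply a calculable false-positive rate for Hypothesis 1.* Such a figure would concern rejecting OR = 1, not reaching 2.5. It would also need an outcome count and an independence assumption that the protocol does not give. The absence of a named outcome stands as a point without it.

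**Conclusion.** The point holds. Hypothesis 1 is a threshold claim, while the sample size that relies on it gives power only against OR = 1. At the planned effect, the lower 95% limit clears 2.5 in 2.5% of studies, and an observed 2.5 has an interval of about 1.6 to 3.8–4.0. The hypothesis would therefore normally be neither verified nor falsified. Excluding 2.5 with 80% power needs a true OR of about 4.5 to 4.9. At a true OR of 2.0 the study would reject OR = 1 in 80–89% of cases, yet could be read as a failed hypothesis if the point estimate is used.

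The missing outcome and the two descriptions of the control group are a lesser part of the same problem: they leave the test of Hypothesis 1 open, but the plan does not specify a pooled analysis.

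These figures assume a null of OR = 1 and a two-sided 5% level (inferred from the formula), 20% prevalence in C2, 150 workers, C2 between 200 and 350, and unadjusted Wald intervals. Confounder adjustment, or any design effect from sampling by square, would widen the intervals. The conclusion is the same across the whole range of C2 sizes.

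**What to change.** Restate Hypothesis 1 along these lines: the odds of any intestinal parasitic infection are higher in W1/W2 than in C2 (H0: OR = 1, two-sided 5%; OR 2.5 is the planning alternative).

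In Section 4.2.1.8.2, name that outcome and contrast for Hypothesis 1, keep C1 out of its control group, and report the OR with its 95% confidence interval. Label the farmer and C1 contrasts and the other outcomes as secondary for this hypothesis. In Section 4.2.1.9, drop the promise to verify or falsify the 2.5 threshold. Bring the abstract's description of the control group into line, and reconcile the C1 and C2 sizes between Section 4.2.1.2 and Table 6.

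The cost is wording only: no extra participants or data, and the power statement stands as power against OR = 1. If the sponsor does want to show that the OR exceeds 2.5, H0: OR ≤ 2.5 would have to be stated and the study sized for it, which the present numbers do not do unless the true OR is well above 4.

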To select the community groups C1 and C2 we will rely on the population data collected in the census 2012 and characterise the low and middle income settlements restricted to an area around the Nakivubo swamp (population estimate and area characterization for C1 is given in Table 5 and Figure 4). We will focus at a total area of approximately 96 km^2^ and subdivide the area in 96 squares (each square 1km^2^) and exclude all areas which belong to ether high income, industrial or business areas. Further we will describe and map the characteristics (income level, numbers of household) of each square and assign it to ether C1, C2. To get the necessary data we will first consult the data from the national bureau of statistic to have a rough understanding of the social-economic pattern, second our team will go and map the households and estimate the number of people living in each square. Later, we will randomly select (with random numbers) 14 squares for C1 and 9 squares for C2. Within each square we will randomly select 25 households and contact the household members personally to ask if they are willing to participate in the study. If they agree we will make an appointment for an interview and will collect the stool sample the next morning (Figure 5).

Table 5 Population sizes of communities (C1) exposed to Nakivubo swamp

| Area | Zones | Social economic status | Population estimate |
| --- | --- | --- | --- |
| Bukasa parish | Keityabya/Yoka | Low | 5,000 |
|  | Soweto/Kanyogoga | Low | 2,500 |
|  | Namuwongo A | Low | 1,500 |
|  | Namowongo B | Low | 3,000 |
| Muyenga |  | High | 1,500 |
| Nakawa | Port Bell | Low | 3,000 |
|  | Kitintale | Middle | 2,000 |
|  | Bugolobi | Middle | 2,000 |
|  |  | Total | 20,500 |

[figure not shown]

**Figure 4** Map showing communities adjacent to Nakivubo swamp

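### The stated 95%/80% power assumes independent participants, but C1 and C2 are drawn as 25 households per square; with no ICC or design effect, that power is not assured

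*Combined protocol and SAP*

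**What the plan says.** Sample size (4.2.1.2): "We conducted a logistic regression analysis having four exposure levels W1/W2, F1, C1 and C2". The target is 95% power, chosen so that "a reduction in effective exposure variance by 35% still leaves 80% power". The reserve is tied to covariate adjustment: "Effective exposure variance is the variance of the 4-level exposure variable after regression on potential confounding variables", with socio-economic status as the example. The chosen scenario (Table 4, scenario 3) takes "an OR between the highest (W1, W2) and lowest exposure group (C2) of 2.5" and has the plan "assume a prevalence rate of intestinal parasitic infections of 20"% in C2. The only other inflation is a non-response margin of 25 for F, 25 for C1 and 50 for C2.

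Sampling (4.2.1.3): 1 km² squares are each assigned to C1 or C2, then 14 are drawn for C1 and 9 for C2. "Within each square we will randomly select 25 households". Table 6 specifies one member per household but reverses the counts, with C1 at 225 in 9 squares and C2 at 350 in 14. Workers and farmers are not sampled by square.

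Analysis (4.2.1.8.2): for Hypothesis 1, "a multilevel regression analyses, adjusting for confounding, will be used". The levels are not named, and the model is not linked back to the sample size.

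**The concern.** People in the same square share water, drainage and sanitation, so their infection status may be correlated. If it is, 25 households from one square carry less information than 25 independent people. Because a square belongs wholly to C1 or C2, variation between squares does not cancel from comparisons with C2. A multilevel model with square as a level would allow for this in its standard errors, but it cannot bring back the power.

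The 35% reserve does not cover this, since the plan has already committed it to confounding. The number of squares is fixed before fieldwork and cannot be raised at analysis. The plan's statement that the small worker group limits power most also assumes that C2 contributes its full nominal size.

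**Working it through.** **Inputs from the plan.** Two-sided alpha 0.05 (implied by 1.96). C2 prevalence 20%; OR 2.5 for W1/W2 versus C2. Calculated sizes (Table 4, scenario 3): F 250, W 150, and 300 and 200 for the two community groups. Two allocations are possible:
- Table 6 order: C2 300 in 14 squares, C1 200 in 9. The text of 4.2.1.2 supports this, since it caps C1 at 200 and leaves C2 free.
- Text order (Table 4 header, 4.2.1.3): C2 200 in 9 squares, C1 300 in 14.

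**Assumption.** The documents give no ICC; 0 to 0.10 is shown.

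**1. The plan's own figure.** (1.96 + 0.84) × 1.25 = 3.5, and 3.5 − 1.96 = 1.54. Φ(1.54) = 93.8%, which the plan calls slightly under 95%. The algebra reproduces.

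**2. Scenario 3 under independence.** A log-linear trend over four equally spaced levels has slope b = ln(2.5)/3 = 0.3054. It gives prevalences of 20.0, 25.3, 31.5 and 38.5%, matching Table 4 to rounding. With C2 = 200, power is 98.3% for the trend, 94.5% for a 3-df test and 96.4% for workers versus C2. After the 35% loss, the trend has 91.0% and the contrast 85.8%. The stated power is met.

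**3. Adding the design effect.** DE = 1 + (m − 1) × ICC for C1 and C2, with m = 300/14 = 21.4 or 200/9 = 22.2; DE = 1 for workers and farmers.

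- Trend: w = n·p·(1 − p)/DE per level, I = Σw(x − x̄)² with x̄ the w-weighted mean, power = Φ(b·√I − 1.96). The 35% loss multiplies b·√I by √0.65.
- Workers versus C2: SE² = DE/(n × 0.2 × 0.8) + 1/(150 × 0.385 × 0.615), power = Φ(ln 2.5/SE − 1.96), with the same √0.65 for the loss.

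Worked example, Table 6 order at ICC 0.05:
- Trend: DE is 2.02 (C2) and 2.06 (C1); w = 23.7, 18.4, 54.0, 35.5 for C2, C1, F, W; x̄ = 1.77; I = 141.8; b·√I = 3.64; power 95.3%. After the loss, 3.64 × 0.806 = 2.93; power 83.5%.
- Contrast: SE² = 0.0421 + 0.0282 = 0.0703, SE = 0.265; 0.916/0.265 = 3.46; power 93.3%. After the loss, 2.79; power 79.6%.

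Power before/after the 35% loss:

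| ICC | Trend, C2 300 in 14 | Trend, C2 200 in 9 | W v C2, 300 in 14 | W v C2, 200 in 9 |
|---|---|---|---|---|
| 0 | 99.3 / 94.6 | 98.3 / 91.0 | 98.5 / 91.6 | 96.4 / 85.8 |
| 0.02 | 98.1 / 90.3 | 96.2 / 85.3 | 96.9 / 86.9 | 92.5 / 78.2 |
| 0.05 | 95.3 / 83.5 | 92.0 / 77.5 | 93.3 / 79.6 | 85.3 / 68.0 |
| 0.10 | 89.4 / 73.4 | 84.6 / 67.0 | 85.7 / 68.5 | 73.4 / 54.9 |

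Full recruitment changes little, because it adds households to the same squares. At ICC 0.05 the contrast has 94.2%/81.2% with C2 = 350 in 14 squares and 86.6%/69.6% with 225 in 9.

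**4. Which group limits power.** At ICC 0.05 the effective C2 size is 300/2.02 = 148 or 200/2.06 = 97, against 150 workers. In the worked contrast, C2 contributes more variance (0.0421) than the workers (0.0282).

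**5. More squares, same total.** With 300 analysed in C2 at ICC 0.10, 28 squares give m = 10.7, DE = 1.97 and 93.6%/80.2% for the contrast, against 85.7%/68.5% with 14.

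**The case against.** A reader might infer that the study is underpowered for Hypothesis 1. The documents do not support that. They give no ICC, and the 95%/80% target is defined on the 4-level exposure variable. With the Table 6 allocation, that trend still meets both figures at ICC 0.05 and keeps 81.3% after the loss at 0.06. This objection stands, so the trend should be reported first. The worker-versus-C2 contrast still matters because Hypothesis 1 is worded that way, but it is not what the stated power most naturally describes.

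The lowest figures, 54.9% to 73.4%, need both ICC 0.10 and the 9-square reading of C2. That reading comes from a separate contradiction within the plan and should not add weight here.

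A reader might also take Hypothesis 2 as evidence of clustering. It posits a decline in egg intensity with distance, handled as a covariate. It does not show residual clustering of prevalence among squares that are all about 2 km away. Excluding high-income, industrial and business areas may reduce between-square variation. Adjusting for socio-economic status, water and hygiene may absorb some of the ICC, so stacking the full 35% loss on an unadjusted ICC may count some variation twice. These points argue for showing a range that includes small values; they do not show the ICC to be zero.

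The multilevel model is already planned. If square is a level, the standard errors are handled and the remaining issue is precision.

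**Conclusion.** The omission is clear on the page: the calculation has no ICC, design effect or cluster term, and its one reserve is assigned to confounding. The size of the consequence is not known. The stated power holds for small ICCs and fails for larger ones. On the Table 6 allocation, the trend meets both targets at ICC 0.05 and falls to 89.4%/73.4% at 0.10. On the text allocation it is already 92.0%/77.5% at 0.05. The worker-versus-C2 contrast is slightly short at 0.05 with 14 squares and clearly short with 9.

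These figures rest on assumed ICCs, equal households per square, scenario 3 prevalences, unclustered workers and farmers, and normal critical values. A small-sample correction for 9 + 14 = 23 squares would lower them somewhat. Confidence is high that the plan omits clustering, and only moderate that a material shortfall would follow.

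**What to change.** 1. Reconcile which community group has 9 squares and which has 14 (4.2.1.2, 4.2.1.3, Table 6), since the answer depends on it.
2. In 4.2.1.2, apply 1 + (m − 1) × ICC to C1 and C2. Restate power, before and after the 35% loss, over an assumed ICC range such as 0.02 to 0.10, for both the 4-level trend and the worker-versus-C2 contrast. Revisit the statement that the worker group is the main limit.
3. In 4.2.1.8.2, name square as the random-intercept level, with workers and farmers entered as unclustered individuals.
4. If the mapping finds enough eligible squares among the 96 and fieldwork allows, keep the C2 total but use more squares with fewer households each. The same applies to C1 as far as its geography permits.

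Items 1 to 3 cost only text and a less favourable stated power. Item 4 adds travel and scheduling. Table 6 allots C2 10 working days, the plan names four assistants, and stool is returned to an appointed health centre the next morning. It is therefore an option to test and not a requirement.
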